**Method:**

In a parallel-group, two-arm, randomized controlled trial, an initial *N* = 178 mothers diagnosed with BPD and their children aged 6 months to 6 years are assigned to either the parenting intervention or a waiting control group. If taking place, participants of both groups continue their regular treatment for BPD diagnosis (e.g., individual therapy, medication). The primary outcomes are changes in parenting from baseline (day 0) to post intervention (week 12) and follow-up (6 months after group intervention; month 9). The waiting control group can attend the group intervention at the end of all assessments. Participants allocated to the intervention group are expected to show improvement in their parenting and a reduction in child abuse potential. Maternal emotion regulation and mental distress are analyzed as secondary outcomes.

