### Trial design

The trial is designed as a randomized, controlled, multi-center trial with two parallel groups. Randomization will be performed as clustered randomization with a 1:1 allocation by RedCap software for each study center separately.

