### Intervention

The manualized group-intervention “Parenting Skills for Mothers with Borderline Personality Disorder” [5, 6] is based on the concept of Dialectical Behavioral Therapy [37, 38]. DBT was developed to treat severe emotion dysregulation in BPD and focuses on the reduction of self-harming behavior, promotes mindfulness, and contains skills training to better cope with stress and high tension. BPD has proven to be effective in the treatment of BPD [2].

The group-intervention “Parenting Skills for Mothers with Borderline Personality Disorder” comprises 12 weekly 2 h-sessions covering the topics Psychoeducation, Mindfulness, Basic Needs of Children, Stress, Stress Management, Structure and Flexibility, Dealing with Conflicts, Dealing with Children’s and One’s Own Emotions, Physical Contact and Expression, Basic Assumptions about Parenting, and Self-Care. In the last session, all topics are summarized. Each session follows the same structure: mindfulness exercise, homework discussion, break, introduction into new topic using a practical exercise, homework for next session, take-home message. In-between sessions, participants are requested to practice newly gained techniques or knowledge in interaction with their children. Each session and the supporting material (i.e., information sheets and homework instructions) are described in detail in the manual.

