### Power analysis and sample size

Because the primary hypothesis concerns the investigation of the effect of the intervention in contrast to the waiting control group, power calculation is based solely on a repeated measure, within-between ANOVA. We strive for a statistical power of 99%; multiple-comparison problems are considered according to Cramer et al. [57]. A conservative estimate of *r* = 0.5 is used for the correlation between repeated measures of the same outcome to ensure enough power for outcomes with relatively low stability over time. Using the software G-Power, these specifications lead to a required sample size of 110 patients (2*55 per group intervention/waiting group) to detect an interaction when Cohen’s *f* for the interactions of 2*3 ANOVA is assumed to be moderate at 0.20. Based on our pilot groups, we assume that 10% of participants assigned to the intervention will not start intervention after assignment. Dropout rates from psychotherapy trials for BPD range between 22.3% and 28.2% [58]. In conclusion, we expect a dropout rate from baseline to follow-up assessment of 25%. Therefore, we assess *n* = 178 mothers with BPD for eligibility (*n* = 160 start the trial, *n* = 140 at post assessment, *n* = 120 at follow-up).

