### Methods: assignment of interventions

Sequence generation: Mothers with BPS are randomly assigned after inclusion to either control or intervention group with a 1:1 allocation as per a computer-generated randomization schedule (RedCap software) stratified by site.

Concealment mechanism: Allocation concealment will be ensured, as study staff will not release the randomization results until the participant has passed the baseline assessments. If randomization is run before baseline assessments, study staff running the randomization differ from those conducting baseline assessments. Otherwise, randomization is run after baseline assessments, and participants are informed via telephone.

When sufficient participants are randomized to the intervention group, personal data (name and phone number) are passed on to the group trainers who contact the group participants. Group trainers do not have access to participants’ study data (diagnosis, questionnaires) or IDs. All intervention material is passed on to the study staff and allocated to the respective ID.

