#### Statistical analyses of intervention effects

Analyses follow the intent-to-treat framework. In particular, we will use linear mixed effects models [59] with their advantages in the handling of missing and longitudinal data to analyze of our primary outcome measures. The respective statistical models will include fixed effects for time, intervention and the interaction of time and intervention as well as random effects for the participants.

Differences in the effectiveness of the intervention across three sites will be investigated. The factor site will be included in all statistical analyses concerning the primary and secondary outcome measures if there are substantive differences.

Additionally, the effect of concomitant interventions will be investigated.

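### The parenting programme is delivered in groups in one arm only, but the stated mixed model and the sample size make no allowance for correlation within therapy groups

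*Protocol article*

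**What the plan says.** - **Delivery.** The Intervention section describes a manualised group programme that "comprises 12 weekly 2 h-sessions covering the topics" listed there.
- **Formation of groups.** Under Methods: assignment of interventions, mothers are "randomly assigned after inclusion to either control or intervention group with a 1:1 allocation as per a computer-generated randomization schedule", with site as stratum. Groups are put together afterwards: "When sufficient participants are randomized to the intervention group, personal data (name and phone number) are passed on to the group trainers".
- **Control arm.** The abstract (Method) says: "The waiting control group can attend the group intervention at the end of all assessments". Control mothers are therefore ungrouped at every analysed time point.
- **Model.** Statistical analyses of intervention effects specifies an intention-to-treat linear mixed model with fixed effects for time, intervention and the "interaction of time and intervention as well as random effects for the participants". Site is added only if sites differ substantively.
- **Sample size.** In Power analysis and sample size, the "power calculation is based solely on a repeated measure, within-between ANOVA". The inputs are 99% power, f = 0.20 and a correlation of 0.5, giving N = 110. No group size, ICC or numeric alpha is given. The plan expects 160 mothers to start, 140 at post assessment and 120 at follow-up.
- **Wording of the allocation.** Trial design says: "Randomization will be performed as clustered randomization with a 1:1 allocation by RedCap software for each study center separately".

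**The concern.** Mothers in one therapy group share trainers, exercises and each other's company for twelve weeks. Their outcomes at week 12 and month 9 may therefore be more alike than those of mothers in different groups. Because only the intervention arm is grouped, this is a partially nested design.

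A random effect for the participant accounts for repeated measures on the same mother, but not for correlation between mothers in a group. With a positive group ICC, the model understates the variance of the intervention-arm mean at post and follow-up. Confidence intervals for the primary contrast are then too narrow, and the test rejects a true null hypothesis more often than its nominal level. Recruiting more mothers into groups of the same size does not remove this error; only the model can. A site factor does not remove it either, because a site would normally run several groups.

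**Working it through.** **1. Reproducing N = 110.** For the within-between interaction with independent participants, three time points and sphericity:

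λ = N·f²·3/(1 − ρ) = 110 × 0.04 × 3/0.5 = 26.4, with df1 = 2 and df2 = 2 × (110 − 2) = 216.

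| Assumed alpha | N for 99% power | Power at N = 110 |
|---|---|---|
| 0.05 | 92 | 99.7% |
| 0.05/3 | 110 | 99.1% |
| 0.01 | 118 | 98.5% |

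The stated 110 is reproduced exactly at alpha = 0.05/3 with independent mothers. That alpha is inferred, since the article mentions a multiplicity adjustment but gives no figure. On this reading, 110 contains no design effect.

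**2. Inflation from one-arm clustering.** With equal arms, groups of size m and intraclass correlation ICC, only the intervention arm carries the design effect. The variance of the arm difference is multiplied by

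VR = [1 + (1 + (m − 1)·ICC)]/2.

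With a correlation of 0.5, change from baseline has variance 2(1 − 0.5)σ² = σ², so the factor also fits a change contrast. The approximate type I error of a nominal 5% test of one contrast is 2·[1 − Φ(1.96/√VR)]. Example, m = 8 and ICC = 0.10: VR = (2 + 0.70)/2 = 1.35, √VR = 1.162, error = 9.2%.

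The values of m and ICC below are assumptions. Power uses N/VR in the formula of step 1 at alpha = 0.05/3, which is an approximation.

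| m | ICC | VR | True SE / reported SE | Type I error | Power, N = 110 | Power, N = 120 |
|---|---|---|---|---|---|---|
| 6 | 0.01 | 1.025 | 1.01 | 5.3% | 98.9% | 99.4% |
| 6 | 0.05 | 1.125 | 1.06 | 6.5% | 98.1% | 98.9% |
| 6 | 0.10 | 1.25 | 1.12 | 8.0% | 96.6% | 97.8% |
| 6 | 0.15 | 1.375 | 1.17 | 9.5% | 94.6% | 96.4% |
| 8 | 0.01 | 1.035 | 1.02 | 5.4% | 98.8% | 99.4% |
| 8 | 0.05 | 1.175 | 1.08 | 7.1% | 97.5% | 98.5% |
| 8 | 0.10 | 1.35 | 1.16 | 9.2% | 95.0% | 96.7% |
| 8 | 0.15 | 1.525 | 1.23 | 11.2% | 91.7% | 94.2% |

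**3. Check by simulation.** The 2-df interaction test was simulated with three time points, correlation 0.5 and a shared group effect at post and follow-up in the intervention arm.
- With 60 per arm and ICC 0.01, 0.05 and 0.10, rejection was 5.34%, 6.38% and 8.12% for m = 6, and 5.24%, 7.10% and 9.45% for m = 8.
- With 55 per arm and ICC 0.05, 0.10 and 0.15, a separate simulation gave 6.6%, 7.5% and 8.7% for m = 6, and 6.8%, 8.6% and 10.9% for m = 8. Without clustering it gave 5.1%.

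These agree with step 2.

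**4. Room in the planned numbers.** The 120 expected at follow-up exceed 110 by a factor of 120/110 = 1.09. That absorbs (m − 1)·ICC up to 2 × 0.0909 = 0.18, which is an ICC of about 0.036 for groups of 6 or 0.026 for groups of 8. Beyond that, power falls below 99%, but slowly.

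**The case against.** **Size is not fixed by the documents.** This stands. Without a group size or an ICC, the type I error may lie anywhere from about 5% to about 11%, and near ICC 0.01 the problem is negligible. A reader might infer that the standard errors are certainly too small; the article supports that only if the ICC is positive.

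**Power.** A reader might infer that the trial is underpowered. It is not: the 99% target leaves ample margin, and at 120 completers power stays at about 94% or more in every case tabulated.

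**Non-starters dilute the clustering.** The plan expects 10% of mothers assigned to the intervention not to start, and they share no group. This is correct but small: repeating the simulation with 6 of 55 intervention mothers ungrouped changed the type I error by less than one percentage point.

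**A condensed article may not list every model term.** A full analysis plan could add one. But the article does state a random-effects structure and a sole basis for the sample size, and neither provides for groups. The point addresses a stated specification.

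**A group variance is hard to estimate from few groups.** With 55 to 80 intervention mothers in groups of 6 to 8 there would be about 7 to 13 groups. The variance estimate would be at or below zero in about 30 to 36% of trials at ICC 0.05 and in about half at ICC 0.01. This is a real cost, and the fix has to provide for it.

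**The word 'clustered'.** A reader might infer from Trial design that clusters were randomised, which would invalidate both model and sample size. The documents do not support this. The same sentence goes on to allocation within each study centre, and the assignment section describes mothers allocated individually, with groups formed later. It is a wording conflict and adds no weight to the modelling point.

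**Conclusion.** The concern holds as a correction to the stated model. The design is partially nested, and the model as written ignores that nesting.

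The consequence depends on a positive therapy-group ICC. For groups of 6 to 8, the nominal 5% type I error is about 5% at ICC 0.01, about 6 to 9% at ICC 0.05 to 0.10, and up to about 11% at ICC 0.15. Correct intervals are about 1 to 2% wider at ICC 0.01 and 6 to 16% wider at ICC 0.05 to 0.10.

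The loss of power is secondary: for ICC 0.05 to 0.10, about 95 to 98% remains at N = 110 and about 97 to 99% at 120 completers. These figures rest on the assumed group sizes and ICCs and on the inferred alpha of 0.05/3.

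**What to change.** 1. **Model.** Record therapy-group membership for every intervention mother. Prespecify a partially nested mixed model: a therapy-group random effect at post and follow-up in the intervention arm only, with controls and never-starters as singletons, and Kenward-Roger or Satterthwaite degrees of freedom. State in advance what is reported when the group variance is estimated at zero.
2. **Sample size.** State the numeric alpha. Either note that 99% power applies without clustering, or restate power over the planned group size and an assumed ICC range.
3. **Wording (minor).** Reconcile the term 'clustered' in Trial design with the individual, site-stratified allocation in Methods: assignment of interventions.

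**Cost.** This needs analysis-plan text, one corrected phrase and one recorded variable. The article does not say that group membership is kept in the study data, but trainers already work from lists of their group's participants, so recording it should need no new assessment. The price is somewhat wider intervals, a slightly lower stated power, and possible boundary estimates with few groups.

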## Methods: participants, interventions, and outcomes

### Study design, recruitment, and eligibility

Participants are recruited via three academic study centers in the German cities of Berlin, Bochum, and Bremen. Each study center cooperates with different in- and outpatient facilities, assisted living facilities, and individual therapists, through which participants with BPD are recruited. Most of these services are covered by the public health insurance, so that we expect the sample to be representative for mothers with BPD living in Germany. All participants will first be screened by a short telephone interview regarding their study eligibility (inclusion and exclusion criteria see below). When meeting the inclusion criteria, participants are invited to a face-to-face diagnostic interview (Structured Clinical Interview for DSM 5; SCID CV & SCID PD; German version: [36]; modules: mood disorders, psychotic symptoms, substance use disorders, anxiety disorders, posttraumatic stress disorder, BPD) to assess BPD symptoms and comorbid diagnosis as well as child-related psychopathology (subproject 2). Staff members who received a 2-day training and are supervised regularly conduct all diagnostic interviews. When still meeting inclusion criteria, participants obtain a personal link to complete several web-based questionnaires. Afterwards, they are invited to a first assessment with their child, where variables of subprojects 2, 3, and 4 are assessed. Participants are then randomized to the intervention or the waiting control group. All questionnaires and assessments are repeated post-interventional (week 12) and at follow-up 6 months later (month 9). After completing all assessment points, mothers randomized to the waiting control group are offered to participate in the parenting program (see also Table 1 SPIRIT schedule of enrollment, interventions, and assessments/participant timeline).

**Table 1 Tab1:** SPIRIT schedule of enrollment, interventions, and assessments

Timepoint	Study period																
	Enrolment		Allocation	Post-allocation													
				Intervention period													
			Basement (day 0)	Week 1	Week 2	Week 3	Week 4	Week 5	Week 6	Week 7	Week 8	Week 9	Week 10	Week 11	Week 12	Post-assessment (week 12)	Follow-up assessment (month 9)
Enrolment																	
Eligibility screen	x																
Informed consent	x																
Randomization BPD		x															
Intervention				x	x	x	x	x	x	x	x	x	x	x	x		
Assessments																	

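### Site stratifies the randomisation, yet it enters the models only if the outcome data show substantive site differences; it should be a fixed part of every model

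*Protocol article*

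**What the plan says.** Three statements in the protocol article bear on this point.

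- **Allocation is within site.** *Methods: assignment of interventions* describes a "computer-generated randomization schedule (RedCap software) stratified by site". *Trial design* agrees on this, with "1:1 allocation by RedCap software for each study center separately". There are three centres (*Study design, recruitment, and eligibility*).
- **The listed model has no site term.** *Statistical analyses of intervention effects* specifies "fixed effects for time, intervention and the interaction of time and intervention as well as random effects for the participants".
- **Site enters conditionally.** The same section continues: "Differences in the effectiveness of the intervention across three sites will be investigated". The next sentence is: "The factor site will be included in all statistical analyses concerning the primary and secondary outcome measures if there are substantive differences".

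No other section commits to site as a covariate.

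**The concern.** A factor that restricts the randomisation is normally carried into the analysis whatever its observed effect, because that is what makes the standard error match the design. Here its inclusion is conditional. The condition follows directly on a look at effectiveness by site, which is a comparison of treatment effects by arm. On the natural reading, the primary model is therefore settled after unblinded outcome results have been seen.

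The trigger also answers a different question. Whether the intervention works differently across centres is a matter of heterogeneity. Whether to condition on site follows from how mothers were allocated. A trial with the same effect everywhere would fail the trigger and leave the stratifier out, even if centres differed strongly in how mothers change over time.

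At stake are the calibration of the primary tests, a little power, and a primary model that a reader can verify was fixed in advance.

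**Working it through.** **The plan's own figure.** *Power analysis and sample size* gives 99% power, r = 0.5, and a Cohen's f "for the interactions of 2*3 ANOVA is assumed to be moderate at 0.20", leading to N = 110. For a within-between interaction with 2 groups and 3 occasions, λ = f²·N·3/(1−r), with df 2 and 2(N−2). At N = 110, λ = 0.04 × 110 × 3/0.5 = 26.4. Alpha is not stated as a number. At an assumed alpha of 0.05/3, power is 0.991 and the smallest even N is 110, so the figure is reproduced. At alpha 0.05 the same inputs need 92. This calculation has no site term, so the point below does not alter N.

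**Inputs for the site check.** From the protocol: three sites, 1:1 within site, r = 0.5, and 120 mothers at follow-up. Assumed: equal sites of 40, complete data, two-sided 5% test, site differences as given below, and a 0.5 SD effect at both later visits. The contrast is the mean of the post and follow-up scores minus baseline.

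**Step 1: level differences.** A constant site level cancels from each mother's change. In simulation with 0.5 SD steps between sites and no difference in change, size was 0.049 without site and 0.049 with it; power was 0.881 both ways.

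**Step 2: differences in change, by formula.** With unit outcome variance and r = 0.5, the change contrast has within-site variance 0.5/2 + 0.5 = 0.75. Stratification balances the arms within site, so the true SE is √(0.75 × 4/120) = 0.158. If sites differ in change by −d, 0, +d, a model without site estimates a variance of 0.75 + 2d²/3. Its SE is too large by the factor k = √[(0.75 + 2d²/3)/0.75], and the true size is 2[1 − Φ(1.96k)].

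| d (SD, assumed) | k | size by formula, site omitted | size simulated, site omitted |
|---|---|---|---|
| 0.2 | 1.018 | 4.6% | 4.6% to 4.8% |
| 0.4 | 1.069 | 3.6% | 3.4% to 3.7% |
| 0.6 | 1.149 | 2.4% | 2.5% |

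The simulated values are for runs without added level differences. At d = 0.4 with 0.5 SD level steps as well, they were 3.2% and 3.4%. With site-by-time always in the model, simulated size at d = 0.4 was 4.4% to 5.4% over four runs of 6,000 or 15,000 trials, consistent with 5% allowing for simulation error.

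**Step 3: power at d = 0.4.** Site included: Φ(0.5/0.158 − 1.96) = 0.885 (simulated 0.876 to 0.889). Site omitted: Φ(0.5/0.158 − 1.96 × 1.069) = 0.857 (simulated 0.844 to 0.858). The loss is about 3 percentage points.

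**Step 4: the rule itself.** Read the trigger as a site-by-intervention test at 5% (an assumed threshold). When effects are equal across sites it fires in about 5% of trials, so the stratifier stays out in about 95%. If site is then added as site-by-time, size at d = 0.4 is 0.038 (0.035 with level steps as well), close to never including it. If the trigger also fires on site differences in change, the rule behaves like always including site (0.044 against 0.044 in the same run).

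**The case against.** The strongest reply is that little is at risk, and much of it stands.

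- **Participant effects already absorb site levels.** Step 1 confirms this. SE inflation computed from the share of outcome variance that site explains in a cross-sectional comparison does not carry over to this model. Only variation in change counts. It follows that a site main effect alone would be no remedy. In trial fits with complete data, the time-by-intervention estimate, SE and p-value were identical to four decimals with and without it; with 25% random follow-up loss, the SE moved by under 0.4%.
- **A reader might infer that choosing the model after seeing data inflates false positives.** The figures do not show this for a choice between no site term and site-by-time. Even taking the smaller of the two p-values gave a size of 0.044 to 0.055. Inflation (0.061 to 0.065 where sites do not differ in change) appeared only when the trigger added a dummy-coded site-by-intervention interaction and the intervention coefficient, now one site's effect, was still read as the overall effect. The article does not say it would do that.
- **A reader might infer that the decision could differ between instruments.** The sentence speaks of all primary and secondary analyses, which reads as one decision.
- **A reader might calculate that the trigger has too little power to be useful.** That needs a significance test and per-site numbers, and the article gives neither.
- **The threshold and the form of the site term may be left to an analysis plan not shown.** Granted, and their absence is not the point. The conditional structure is stated in the article, and defining the threshold elsewhere would leave the model dependent on the data.

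**Conclusion.** The point holds at moderate severity. The article stratifies by site, omits site from its default model, and lets outcome results decide whether it comes back. By default the stratifier is ignored; where the condition is met, it is not.

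The expected error is conservative. At assumed site differences in change of -0.4, 0 and +0.4 SD, size is about 3.5% instead of 5% and power about 0.85 instead of 0.88. With smaller site differences the effect shrinks, and with pure level differences it vanishes.

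The power loss also depends on the assumed 0.5 SD effect. The plan's f = 0.20 is larger on this scale: for an effect equal at both later visits, λ = d²N/3 = f²·N·3/0.5, so d² = 18 × 0.04 = 0.72 and d = 0.85 SD. At that effect, power exceeds 0.99 with or without site.

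Nothing here threatens the trial's conclusion, and a reader should not take it as a threat to validity. The reason to act is that the primary model should be fixed before outcomes are seen and should match the allocation, and doing so costs almost nothing.

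**What to change.** Replace the conditional sentence in *Statistical analyses of intervention effects* with:

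> *Site (three levels) and site × time are fixed effects in all primary and secondary models regardless of observed differences. Heterogeneity of the intervention effect by site (site × intervention × time) is reported as exploratory and does not alter the primary model.*

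The site × time term is the part that does the work. The cost is one sentence and a few degrees of freedom: 2 for site and 4 for site × time in the full model, which is 2 of about 118 residual degrees of freedom on any one change contrast. The sample size, data collection and listed outcomes are unchanged.
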